## 4 Trial design

4.1 Randomisation: patients who met the inclusion criteria and signed the informed consent

were randomly grouped into a synchronous radiotherapy group (experimental group) and a chemotherapy-only group (control group) in a 1:1 ratio.

4.2 The protocol of the experimental group: one cycle of induction chemotherapy (SOX) was administered 21 days before radiotherapy; the specific dosage of SOX was S-1 30-40mg/m^2 bid D1-14, oxaliplatin 130mg/m^2 D1,Q3W, and then S-1 simultaneous radiotherapy was started, and the dosage of S-1 was 50mg bid during the period of simultaneous radiotherapy, which was used in combination with radiotherapy for 5 days a week for a consecutive period. in combination, 5 days per week for 28 days. After 3-4 weeks of radiotherapy, the SOX regimen was administered for 3 cycles at the same dose as the induction chemotherapy.

4.3 Control regimen: A total of 6 cycles of SOX regimen (at the same dose as in the experimental group) will be given.

4.4 Radiotherapy: radiotherapy was started within 3 months after surgery. The radiotherapy dose was 50.4 Gy/28f, 1.8 Gy/d, 5f/w. Radiotherapy was given on the 1st-5th day of each week for 28 consecutive days; radiotherapy was given by three-dimensional conformal radiotherapy (3D-CRT) or intensity-modulated radiotherapy (IMRT).

i. Radiotherapy localisation: fasting for 4 hours before localisation; supine position, hands on elbows, body mould fixation, CT simulation localisation, enhanced scanning, scanning range from T6 lower edge to L4 lower edge, layer thickness 3mm.

ii. Radiotherapy target zone (CTV) reference: postoperative radiotherapy target zone of gastric cancer includes tumour bed, anastomosis and regional lymph nodes. For the specific outlining method of target area, refer to 'Annex 1 Specification for Outlining Target Area of Postoperative Radiotherapy for Gastric Cancer' provided in this protocol.

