iii. Radiotherapy plan: 3D-CRT or IMRT technology is used; PTV is externally applied in the anterior-posterior and left-right directions by 0.8 cm on the basis of CTV, and externally applied in the up-and-down direction by 1.0 cm; 95% of the PTV has a minimum dose of 50.4 Gy/28f; hotspot dose is  $\leq 107\%$  of the prescribed dose, and the volume is  $\leq 2$  CC; the target area conformity is  $\geq 0.8$ ; spinal cord is  $\leq 40$  Gy, and the liver V30 is  $\leq 33\%$  of the dose. The maximum dose received by 33% of the volume of one kidney (mostly right kidney) is  $<15$  Gy, and the average of both kidneys is  $<15$  Gy; D50 of small intestine is  $<20-30$  Gy.

4.5 Effectiveness evaluation: patients should undergo effectiveness evaluation at least once every 6 months during the first year after enrolment; after the end of treatment, regular follow-up and effectiveness evaluation should be conducted in accordance with the requirements of the supervising physician, and effectiveness evaluation should be conducted

at least once every 6-12 months. The time intervals of the evaluation should all be referenced to the point in time when the patient was randomised to the group. The evaluation includes physical examination, imaging (CT, chest radiograph, ultrasound, etc.) and laboratory tests (routine blood, blood biochemistry, tumour markers, etc.). The primary study endpoint was 3-year DFS, which was defined as the time from randomisation to the occurrence of tumour recurrence/metastasis (i.e., disease progression), or death in the randomised group; the secondary study endpoint of 3-year OS referred to the time from randomisation to death; and safety was also included.

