## **5 Selection of Patients**

### **5.1 Inclusion Criteria**

- (1) Age 18-70 years;
- (2) Gastric cancer patients who have been diagnosed by pathology and have been surgically resected;
- (3) Surgery is radical, achieving R0 resection, and D2 lymph node dissection (with organ preservation) (the number of lymph node dissection should be  $\geq 15$ );
- (4) The time to surgery is not more than 3 months;
- (5) According to the 2010 edition of UICC/AJCC staging criteria, postoperative pathological stage T stage  $\geq$  T4a, N stage  $\geq$  N0; and no tumour metastasis or postoperative recurrence is detected by comprehensive examination, i.e., the M stage is M0;
- (6) ECOG PS score: 0-1;
- (7) Patients who have not received radiotherapy and systemic chemotherapy before or after surgery;
- (8) Normal function of major organs, i.e., the following indications are met:
  - i. routine blood tests need to meet the following criteria: HB  $\geq$  9g/dL, WBC  $\geq$  3.5/4.0 $\times$  10^9/L, PLT  $\geq$  100 $\times$  10^9/L
  - ii. Biochemical tests must meet the following criteria: Crea and BIL  $\leq$  1.0 times the upper limit of normal (ULN), ALT and AST  $\leq$  2.5 times the upper limit of normal (ULN).
- (9) Women of childbearing potential must have had a negative pregnancy test (serum or urine) 7 days prior to enrolment and be willing to use an appropriate method of contraception for the duration of the trial and for 8 weeks after the last dose. For males, surgical sterilisation should be applied or agreement to use an appropriate method of contraception for the duration of the trial or 8 weeks after the final dose.
- (10) Subjects voluntarily enrolled in the study, signed an informed consent form, were compliant, and cooperated with follow-up.

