## **11 Study Treatment Controls and Assurance**

### **11.1 Quality control measures:**

- (1) All investigators should enrol and treat patients in strict accordance with the trial plan.
- (2) The grading of all toxic reactions should be judged according to the grading criteria specified in the trial.
- (3) The outlining of the radiotherapy target area, and the preparation requirements before radiotherapy, etc. should be carried out in strict accordance with the provisions of Oncology Radiotherapy.
- (4) Inform the subjects of the possible adverse reactions during the trial, and the treatment methods to be adopted in case of adverse reactions.

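### Inclusion criterion 9 joins the two contraception periods with 'or' for men and 'and' for women: a minor safety-wording error, probably a slip

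*Protocol*

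**What the plan says.** Criterion 9 in Protocol section 5.1 has two consecutive sentences on contraception. Women of childbearing potential must "be willing to use an appropriate method of contraception for the duration of the trial and for 8 weeks after the last dose". Men must either be surgically sterilised or give "agreement to use an appropriate method of contraception for the duration of the trial or 8 weeks after the final dose". The Inclusion Criteria row of the synopsis (section 1) has the same pair, with the same difference in connective.

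Three other parts of the protocol bear on how the male sentence works in practice:

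- **Treatment.** Sections 4.2 to 4.4 set the regimens by arm, with no distinction by sex.
- **Length of the trial.** Section 4.5 says that "after the end of treatment, regular follow-up and effectiveness evaluation should be conducted", and section 9.1 has adverse events recorded until protocol-defined follow-up is complete.
- **Adherence.** Section 11.1 (1) states: "All investigators should enrol and treat patients in strict accordance with the trial plan".

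**The concern.** Both sentences use the same building blocks: the length of the trial, and 8 weeks after dosing stops. Only the connective differs. With 'and', both periods must be covered. With 'or', either one is enough on a literal reading, and one of the two begins only when treatment has finished.

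At stake is the protection of partners and offspring while a man receives S-1 and oxaliplatin, with abdominal radiotherapy as well in the SOXRT arm. The protocol recognises reproductive harm as an outcome, because section 9.1 counts a congenital anomaly or birth defect among the criteria for a serious adverse event. The sentence is an operative eligibility rule in a multicentre trial, so it should not depend on each site guessing what was meant.

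**Working it through.** No figure in the plan needs reproducing. The check is a comparison of wording, followed by what each reading would require.

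**Step 1: compare the two sentences.** Women: trial *and* 8 weeks after the last dose. Men: trial *or* 8 weeks after the final dose. The 8-week figure is the same. Section 5.1 and the synopsis agree with each other, so neither corrects the other.

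**Step 2: look for a reason for the difference.** None is given. The SOX arm rule is "A total of 6 cycles of SOX regimen (at the same dose as in the experimental group) will be given". The SOXRT arm has induction ("one cycle of induction chemotherapy (SOX) was administered 21 days before radiotherapy"), S-1 with radiotherapy ("The radiotherapy dose was 50.4 Gy/28f, 1.8 Gy/d, 5f/w"), and then "the SOX regimen was administered for 3 cycles at the same dose as the induction chemotherapy". None of this varies by sex.

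**Step 3: list what lies before the final dose.**

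- SOX arm: 6 SOX cycles (section 4.3).
- SOXRT arm: 1 + 3 = 4 SOX cycles (section 4.2), plus 50.4 Gy / 1.8 Gy = 28 fractions given with S-1 (sections 4.2 and 4.4).

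**Step 4: apply each reading of the male sentence.**

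| Reading of 'or' | Treatment covered? | 8 weeks after final dose covered? |
|---|---|---|
| Choice of periods; man chooses the post-dose period only | No | Yes |
| Choice of periods; man chooses the trial only, and the trial ends at the last dose | Yes | No (8 weeks short) |
| Choice of periods; man chooses the trial only, and the trial includes follow-up | Yes | Yes |
| Two possible stop dates for cover that starts at enrolment; trial includes follow-up | Yes | Yes, under either stop date |
| Two possible stop dates for cover that starts at enrolment; trial ends at the last dose | Yes | Only if the later stop date is used |

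Only the first row leaves the treatment in step 3 uncovered. The rows that assume the trial ends at the last dose fit poorly with sections 4.5 and 9.1, both of which carry the trial into follow-up.

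**Step 5: check the female rule as a model.** Criterion 9 does not define the duration of the trial. If the trial includes follow-up, the added 8 weeks will ordinarily be redundant for women, and the rule asks for contraception throughout follow-up. Copying it to men would make the two sentences agree but would carry over that lack of clarity.

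**The case against.** The strongest case on the other side is that the male sentence can be read as naming two possible end points for contraception that begins at enrolment. Every cycle and every fraction is then covered. This is at least as natural as supposing that a site would accept contraception only after treatment. The protocol also points to a trial that continues into follow-up, so a man who covers only the trial also covers the 8 weeks. The consent form, which section 12 describes as an appendix to the protocol, was not available and may state the rule correctly. The general instruction in section 11.1 does not show which reading sites would adopt, and identical dosing does not by itself prove that the two sexes need identical windows.

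Most of this stands. It limits the likely consequence but does not remove the mismatch: the same criterion uses different connectives for the same two periods, without a reason, and one permissible reading defeats the purpose of the rule.

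A reader might go further and infer that men in this trial will be treated without contraception, and might take 6 cycles, or 4 cycles and 28 fractions, as the size of the harm. The documents do not support that. Those counts describe what the least plausible reading would leave uncovered. They do not show that any site reads the rule that way.

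**Conclusion.** The wording is wrong as it stands, in both places, and the error is minor. The mismatch itself is certain from the text. That it is a drafting or translation slip is probable, given the shared 8-week figure and the absence of any rationale, but it is not proven.

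The safety consequence depends on the reading. Treatment is uncovered only if a man may choose the post-dose period alone. The shortfall is at most 8 weeks if he covers the trial only and the trial ends at his last dose. There is none if he covers the trial and it includes follow-up, as sections 4.5 and 9.1 indicate. The documents give no basis for estimating how many men, if any, would be affected.

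Randomisation, endpoints, sample size and analysis are unaffected.

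**What to change.** The least change is to replace 'or' with 'and for' before the 8-week period in the male sentence, in section 5.1 (9) and in the synopsis.

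A clearer change is to give both sexes one window tied to treatment, for example: *throughout study treatment and until at least 8 weeks after the last dose*. This removes the dependence on an undefined trial duration and settles the female rule at the same time. For the SOXRT arm, the amendment should make plain that study treatment includes radiotherapy.

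If the consent form carries the same wording, it needs the same edit. The cost is a small text change in two places, plus the consent form where applicable, with the ethics committee approval that section 7 requires for any protocol modification. There is no effect on design or analysis, and the effect on recruitment should be negligible.

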## 5.2 Exclusion Criteria

- (1) Previous or concurrent other malignancies, except cured basal cell carcinoma of the skin and carcinoma in situ of the cervix;
- (2) Pregnant or breastfeeding women;
- (3) Patients with severe cardiovascular disease and diabetes that cannot be easily controlled;
- (4) People with mental disorders;
- (5) People with serious infections;
- (6) Hypersensitivity to S-1 or platinum oxalate;
- (7) Serious gastrointestinal diseases that affect the absorption of oral chemotherapeutic drugs
- (8) Participation in another clinical trial within 4 weeks prior to the start of treatment.

## 5.3 Reduction and discontinuation of treatment

- 5.3.1 Patients can voluntarily withdraw from the study at any time.
- 5.3.2 In the event of a 3 or 4 grade haematological toxicity, the next cycle of chemotherapy needs to be given after the toxicity has returned to 0-1 grade and the dose of the next cycle of chemotherapy, S-1, is reduced by 25%.
- 5.3.3 In the event of  $\geq 2$  grade of non-haematological toxicity, chemotherapy should be delayed by 1 week. In the event of 4 grade toxicity during concurrent radiotherapy, other than alopecia, chemotherapy is discontinued and radiotherapy is continued whenever it is considered to be chemotherapy-related.
- 5.3.4 Discontinue radiotherapy only if radiotherapy-associated 3 grade skin inflammation occurs, until toxicity returns to 0-1 grade. If the patient's recovery period requires more than 3 weeks, treatment should be discontinued and the patient discharged from the group.
- 5.3.5 Toxicity was graded according to CTCAE 4.0 criteria.

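### Outside concurrent radiotherapy, Section 5.3.3 gives grade 2, 3 and 4 non-haematological toxicity the same action, a one-week delay with no explicit recovery grade, and its grade 4 rule reaches no SOX cycle in either arm

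*Protocol*

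**What the plan says.** Section 5.3 of the Protocol sets the rules for changing or stopping treatment.

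- **Haematological toxicity, grade 3-4 (5.3.2):** "the next cycle of chemotherapy needs to be given after the toxicity has returned to 0-1 grade", and S-1 is reduced by 25% in that cycle.
- **Non-haematological toxicity, grade 2 or higher (5.3.3, first sentence):** "grade of non-haematological toxicity, chemotherapy should be delayed by 1 week".
- **Grade 4 (5.3.3, second sentence):** "In the event of 4 grade toxicity during concurrent radiotherapy, other than alopecia, chemotherapy is discontinued and radiotherapy is continued", provided the toxicity is judged to come from chemotherapy.
- **Radiotherapy skin toxicity, grade 3 (5.3.4):** radiotherapy is interrupted until grade 0-1. The next sentence says that if the "recovery period requires more than 3 weeks, treatment should be discontinued and the patient discharged from the group".

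Sections 4.2 and 4.3 set the schedule. In the SOXRT arm, "one cycle of induction chemotherapy (SOX) was administered 21 days before radiotherapy"; S-1 without oxaliplatin accompanies the radiotherapy; afterwards "the SOX regimen was administered for 3 cycles at the same dose as the induction chemotherapy". For the control arm: "A total of 6 cycles of SOX regimen (at the same dose as in the experimental group) will be given".

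**The concern.** Section 9.2 grades toxicity from mild to fatal, with grade 2 moderate and grade 4 life-threatening. During SOX cycles, 5.3.3 attaches the same written response to both. The protocol is stricter in the two rules on either side: 5.3.2 and 5.3.4 each name grade 0-1 as the point at which treatment may resume.

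The escalation for grade 4 is tied to the phase in which S-1 is given with radiotherapy. It does not apply when S-1 is given with oxaliplatin, which is all of the control arm's treatment and most of the chemotherapy cycles in the SOXRT arm.

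What is at stake is patient safety and uniform conduct. Section 6 calls for treatment in strict accordance with the study's methods, and Section 11.1 repeats this for all investigators. A physician who does more than 5.3.3 asks has no dose rule to cite. One who does only what it asks may give the next cycle before a severe toxicity has resolved. In a multicentre trial the same event could be handled differently from centre to centre.

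**Working it through.** No power, alpha or event count enters this point. The check sets the rules against the treatment schedule.

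**Step 1. Which SOX cycles can the grade 4 sentence reach?**

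- SOXRT arm (4.2): 1 cycle before radiotherapy + 3 cycles after = 4 SOX cycles. The concurrent phase uses S-1 alone (50 mg twice daily). SOX cycles inside that phase: 0 of 4.
- Control arm (4.3): 6 SOX cycles and no radiotherapy. SOX cycles inside a concurrent phase: 0 of 6.

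If a grade 4 event in the concurrent phase ends chemotherapy for good, that patient's 3 later SOX cycles are also lost. The triggering event must still arise during radiotherapy, so toxicity arising in a SOX cycle is not covered.

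**Step 2. What action does the text state for each type of toxicity?**

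| Toxicity | Setting | Stated action | Stated recovery grade |
|---|---|---|---|
| Haematological, grade 3-4 | Chemotherapy cycles | Wait, then S-1 reduced by 25% | 0-1 |
| Non-haematological, grade 2 | SOX cycle | Delay 1 week | None |
| Non-haematological, grade 3 | SOX cycle | Delay 1 week | None |
| Non-haematological, grade 4 | SOX cycle | Delay 1 week | None |
| Grade 4 except alopecia, chemotherapy-related | Concurrent radiotherapy | Chemotherapy discontinued, radiotherapy continued | None |
| Skin, grade 3, from radiotherapy | Radiotherapy | Radiotherapy interrupted | 0-1 |

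**Step 3. Does another section fill the gap?**

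- Section 5.1(8), "Normal function of major organs, i.e., the following indications are met", lists blood count and biochemistry limits. They are conditions for enrolment, not for starting a later cycle.
- Sections 9.1 and 9.2 cover definition, grading, reporting and follow-up of events. Section 9.1 mentions dose adjustment and stopping only as examples of intervention for a laboratory abnormality.
- Section 11.1(4) is about telling patients how adverse reactions will be treated. It sets no dose rule.

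**Step 4. Do milder readings close the gap?**

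- *The delay repeats while toxicity stays at grade 2 or higher.* This implies recovery to grade 0-1 before retreatment. Grade 4 still gets no action that grade 2 does not.
- *Discontinued in the grade 4 sentence means a temporary hold.* This narrows the contrast between phases. The sentence still does not apply to SOX cycles.
- *The three-week limit in 5.3.4 covers all treatment.* It would then end treatment for slow recovery at any grade. A grade 4 event that settles within three weeks would still be handled like a grade 2 event.

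One smaller point: the delay sentence has no exemption for alopecia, although the grade 4 sentence next to it has one.

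**The case against.** The strongest reply is that 5.3.3 is terse rather than unsafe. Its trigger is a state, grade 2 or higher. If that state persists after a week, the condition is still met and the delay applies again, so recovery to grade 0-1 is implied. This is a plausible reading, and it is why the point is the lack of an *explicit* recovery grade. It does not answer the grade 4 part.

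A reader might also infer three stronger claims that the documents do not support.

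- *That 5.3.3 obliges investigators to retreat after a week.* It orders a delay. It neither orders retreatment nor forbids stopping, and other sections plainly contemplate clinical action on adverse events. The most the text supports is that a patient may be retreated.
- *That identical toxicity permanently ends chemotherapy in one phase and not in the other.* Section 5.3.4 uses the same verb first for a pause until grade 0-1 and then for a final stop. In the grade 4 sentence its meaning is open.
- *That patients will be harmed at some estimable rate.* The protocol gives no rate of grade 2-4 non-haematological toxicity for SOX alone. Section 8.1 reports a low grade 3/4 incidence and no life-threatening event, though for SOX with radiotherapy and not for six cycles of SOX alone. Section 9.1 adds 24-hour reporting of serious events and follow-up until they resolve or stabilise.

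These arguments limit the severity but do not remove the point. Nor is this something left to a statistical analysis plan: dose modification is a treatment rule, and this protocol sets it.

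**Conclusion.** The point holds in a limited form. Outside concurrent radiotherapy, the written action for non-haematological toxicity is the same at grades 2, 3 and 4, and the grade 4 sentence applies to none of the SOX cycles counted above. The absence of a distinct grade 4 action does not depend on how the ambiguous wording is resolved. The possibility of retreatment before recovery does: it arises only if the one-week delay is not read as repeating.

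This is a stated safety rule that is inadequate if followed strictly, so it should be fixed. Its severity is moderate. The conclusion rests on the text of Sections 4.2, 4.3 and 5.3 and on there being no retreatment rule elsewhere in the protocol. It says nothing against the trial's sample size or its primary comparison of DFS.

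**What to change.** Amend 5.3.3 as follows, for both arms:

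1. The next SOX cycle is given only after non-haematological toxicity, alopecia exempt, has returned to grade 0-1. This is the threshold 5.3.2 already uses.
2. State an action for chemotherapy-related grade 4 non-haematological toxicity arising in a SOX cycle. The minimum is to withhold chemotherapy until grade 0-1. Whether to stop permanently or reduce the dose, by how much and for which drug, is for the investigators to decide.

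Also state whether the three-week limit in 5.3.4 applies to SOX cycles or only to the radiotherapy skin rule before it.

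A mandatory permanent stop for grade 4 in every phase, or a three-week limit on all treatment, would be a clinical trade-off going beyond this defect and is not proposed here.

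The cost is a short amendment with ethics committee approval (Section 7). The downside is some longer delays and some lost adjuvant cycles, including in patients whose grade 2 toxicity is slow to settle.

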## **9 Adverse Events**

- 9.1 Definition of AE  
An Adverse Event (AE) refers to any undesirable medical occurrence in a study participant that coincides with the administration of an investigational drug, regardless of its causal relationship. This encompasses any unfavorable or unintended symptoms, signs, or medical conditions, whether treatment-related or not, including laboratory abnormalities necessitating clinical intervention (e.g., dose adjustment or treatment discontinuation). AEs are recorded from the moment informed consent is obtained until the completion of the protocol-defined follow-up period.

A Serious Adverse Event (SAE) is an AE that meets at least one of the following criteria: results in death, poses an immediate life-threatening risk, necessitates hospitalization or extends an existing hospital stay, leads to significant or persistent

disability/incapacity, involves a congenital anomaly or birth defect, or is deemed a medically critical event requiring intervention to prevent these outcomes. All SAEs must be reported within 24 hours of awareness, irrespective of causality. Investigators are responsible for assessing the potential relationship between the intervention and the event, ensuring thorough documentation and follow-up until resolution or stabilization.

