## 9.2 Assessment of AE

All toxicity evaluations are evaluated based on the Common Terminology Criteria for Adverse Events (CTCAE) v4.0, published by the U.S. National Cancer Institute (NCI). The CTCAE v4.0 provides standardized grading criteria for AEs, categorizing their severity from Grade 1 to Grade 5, defined as follows: Grade 1 = mild, Grade 2 = moderate, Grade 3 = severe, Grade 4 = life-threatening, and Grade 5 = death. Radiotherapy-related adverse events are assessed using the Radiation Therapy Oncology Group (RTOG) Acute Radiation Morbidity Scoring Criteria from the initiation of treatment until 28 days post-radiation. Evaluations are conducted weekly during therapy and biweekly during follow-up, incorporating clinician-reported outcomes and patient-reported symptom diaries. The primary assessment domains include: dermatologic toxicity, mucosal injury, gastrointestinal toxicity, pulmonary complications.

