### **III. Radiotherapy Planning**

1. 3D-CRT, IMRT should be used;
2. Based on the CTV, the PTV should be expanded by 0.8 cm in the anterior, posterior, left, and right directions, and by 1.0 cm in the cranial-caudal direction;
3. Minimum dose covering 95% of the PTV: 50.4 Gy in 28 fractions; hotspot dose  $\leq$  107% of the prescription dose, with hotspot volume  $\leq$  2 cc;
4. Conformity index (CI)  $\geq$  0.8;
5. Dose constraints for major organs at risk: spinal cord  $\leq$  40 Gy, liver V30  $\leq$  33%, the dose to 33% of the volume of one kidney (most commonly the right kidney)  $<$ 15 Gy, mean dose to both kidneys  $<$ 15 Gy; small bowel D50  $<$ 20-30 Gy.

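### As worded, section 5.3.4 allows a radiotherapy hold only for grade 3 skin inflammation, and no hold is written for severe mucosal, gastrointestinal or pulmonary radiotherapy toxicity

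*Protocol*

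**What the plan says.** Section 5.3 of the protocol sets the rules for reducing and stopping treatment.

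- **5.3.2** concerns grade 3 or 4 haematological toxicity. The next chemotherapy cycle waits for recovery to grade 0-1, and S-1 is cut by 25%. Radiotherapy is not mentioned.
- **5.3.3, first sentence,** delays chemotherapy by 1 week for non-haematological toxicity of grade 2 or higher, whatever its cause.
- **5.3.3, second sentence,** covers grade 4 toxicity (other than alopecia) during concurrent radiotherapy: "chemotherapy is discontinued and radiotherapy is continued whenever it is considered to be chemotherapy-related".
- **5.3.4** is the radiotherapy rule: "Discontinue radiotherapy only if radiotherapy-associated 3 grade skin inflammation occurs", until recovery to grade 0-1. A second sentence adds that if the "recovery period requires more than 3 weeks, treatment should be discontinued" and the patient leaves the group.
- **5.3.5** grades toxicity by CTCAE 4.0.

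Section 9.2 scores radiotherapy-related events on the RTOG acute criteria and names the main domains as "dermatologic toxicity, mucosal injury, gastrointestinal toxicity, pulmonary complications". On timing it says "Evaluations are conducted weekly during therapy and biweekly during follow-up". Section 8.1 lists the main expected effects. They are gastrointestinal symptoms, fatigue and low leukocyte or platelet counts; skin reaction is not on the list.

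**The concern.** The radiotherapy rule does not match the protocol's own safety sections. The one toxicity that triggers a hold is not among the main effects expected in 8.1. The gastrointestinal effects that are expected, and the mucosal and pulmonary domains that 9.2 monitors, trigger none.

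The field is the upper abdomen. Appendix 2 (III, item 5) opens with "Dose constraints for major organs at risk: spinal cord" and goes on to limit the dose to liver, kidneys and small bowel. These are planning limits and say nothing about event rates, but they show that bowel exposure is foreseen.

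Patient safety and consistency between sites are at stake. Sections 6(2) and 11.1(1) require strict adherence to the protocol. A site that follows 5.3.4 to the letter would have no permission to pause radiotherapy for a severe radiation-related bowel, mucosal or lung event. A site that reads it more loosely must set its own threshold and restart point, and cannot tell whether the 3-week limit applies.

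**Working it through.** The plan gives no figure to reproduce. The check is a comparison of the rules, with a little arithmetic for scale.

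**Step 1. Which rules act on radiotherapy?**

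| Rule | Trigger | Action on chemotherapy | Action on radiotherapy |
|---|---|---|---|
| 5.3.2 | Haematological, grade 3-4 | Wait for grade 0-1; S-1 down 25% | None stated |
| 5.3.3, first sentence | Non-haematological, grade 2 or higher, any cause | Delay 1 week | None stated |
| 5.3.3, second sentence | Grade 4 in concurrent phase, chemotherapy-related | Stop | Continue |
| 5.3.3, second sentence | Grade 4 in concurrent phase, radiotherapy-related | None stated in this sentence | None stated |
| 5.3.4 | Radiotherapy-associated skin inflammation, grade 3 | None stated, unless recovery exceeds 3 weeks | Hold to grade 0-1; stop if recovery exceeds 3 weeks |

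Sections 4.2 to 4.4, 8, 9.1, 9.2, 11 and Appendix 2 contain no further toxicity rule for holding radiotherapy. Voluntary withdrawal (5.3.1) is not a toxicity rule.

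**Step 2. Set the rules against the monitored domains.** Section 9.2 names 4 domains: skin, mucosal, gastrointestinal and pulmonary. A radiotherapy hold is written for 1 (skin) and for none of the other 3. Within skin the text names grade 3; whether grade 4 is included is left to the reader.

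**Step 3. Test both readings of the word 'only' in 5.3.4.**

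- *Sole condition:* radiotherapy may be held if, and only if, there is grade 3 skin inflammation. A hold for any other toxicity is excluded.
- *Radiotherapy alone:* in that event, stop radiotherapy and not chemotherapy. Other holds are not excluded, but none is written.

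Under both readings the mucosal, gastrointestinal and pulmonary domains have no radiotherapy threshold and no restart criterion. The 3-week sentence does not name skin, so it may reach further, but it sets no trigger for a hold.

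**Step 4. Scale.** Section 4.4 states: "The radiotherapy dose was 50.4 Gy/28f, 1.8 Gy/d, 5f/w".

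- Total: 28 x 1.8 = 50.4 Gy, as stated.
- One further week without a hold: 5 x 1.8 = 9.0 Gy, and 9.0 / 50.4 = 17.9% of the prescription.
- Illustration: for an event after 15 fractions, 15 x 1.8 = 27.0 Gy has been given. 13 x 1.8 = 23.4 Gy (46.4%) remains.
- Patients to whom the rule applies: 620 / 2 = 310, from the 1:1 allocation.
- Each 1% with such an event would be 310 x 0.01 = 3.1 patients.

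The domain count measures rule coverage and the doses restate the prescription. Neither measures risk. Section 8.1 describes grade 3/4 toxicity in phase I/II as low in incidence and gives no rates, so the number affected cannot be computed.

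**The case against.** The strongest objection comes from 5.3.3. Its instruction to continue radiotherapy at grade 4 depends on the event being chemotherapy-related. If radiotherapy could never be held except for skin inflammation, that condition would have no purpose. The two rules then look like a pair: for a chemotherapy-related event stop chemotherapy and keep radiotherapy, and for a radiotherapy-related skin event stop radiotherapy alone. The text also reads like a translation, so the position of one word carries limited weight. This gives real support to the less restrictive reading. It does not supply the missing rule, and it leaves grade 3 non-skin toxicity open.

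A second objection is that the protocol has other safeguards.

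- The 1-week chemotherapy delay in 5.3.3 already applies to mucosal, gastrointestinal and pulmonary toxicity from grade 2, so these events do lead to a treatment change. It is not a radiotherapy change.
- Section 9.1 speaks of "clinical intervention (e.g., dose adjustment or treatment discontinuation" in connection with laboratory abnormalities, so clinical judgement is not excluded.
- Section 9.2 requires weekly evaluation, 11.2(3) makes the study lead answerable for subjects' interests, and section 12 invokes the Helsinki declaration.

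These make it likely that a clinician would act. None says when to hold radiotherapy or when to restart.

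A reader might infer that the protocol obliges sites to irradiate through a severe bowel or lung event, or that 5.3.3 orders radiotherapy to continue for radiotherapy-related grade 4 events. The documents do not support either as a settled fact. The first depends on one of two readings, and against it stand the safeguards above. The second misreads a clause that covers chemotherapy-related events only.

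**Conclusion.** The point stands in a limited form. As worded, 5.3.4 permits a radiotherapy hold only for grade 3 radiotherapy-associated skin inflammation. No hold is written for severe radiotherapy-related mucosal, gastrointestinal or pulmonary toxicity, which is 3 of the 4 domains that 9.2 monitors. The gap remains under either reading of 'only'; the reading decides whether such holds are barred or merely unregulated.

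It should be corrected because it is a safety rule in a multicentre trial and the correction is cheap. Confidence is medium, because the wording allows two readings and clinicians would probably act anyway.

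A reader might also infer frequent harm, or a bias in the DFS comparison. Neither is shown: the protocol gives no event rates, and nothing in it links this rule to the primary endpoint, the sample size or the analysis. Toxicity management belongs in the protocol and is already fixed in 5.3, so a separate analysis plan would not be expected to fill the gap.

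**What to change.** Replace the first sentence of 5.3.4 with: *Hold radiotherapy for radiotherapy-related toxicity of grade 3 or higher (CTCAE 4.0) of skin, mucosa, gastrointestinal tract or lung until it returns to grade 0-1; if recovery takes more than 3 weeks, stop protocol treatment but keep the patient in DFS and OS follow-up in the randomised arm.* This takes over the present 3-week sentence, which should then be deleted. The clinical investigators should confirm the threshold for each domain.

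Two details matter.

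- **Grading scale.** It must be named, because 5.3.5 uses CTCAE 4.0 while 9.2 scores radiotherapy events by RTOG.
- **Follow-up.** The present rule has patients leave the group after 3 weeks. Extending it to more toxicities in the SOXRT arm alone could add one-sided losses, and section 10.3 already plans for 20% of patients to be left out of the statistics. Keeping these patients in follow-up avoids that.

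The cost is a short amendment with ethics committee approval, some clinical input on thresholds, and somewhat more radiotherapy interruptions in the SOXRT arm.
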